| 1. Has this protocol been peer reviewed by another Committee?   Yes* xNo  ** Please state in your protocol the name of the reviewing Committee(s) and provide an outline of the review process and outcome. NIHR Health Services and Delivery Research Programme* |
| 1. Type of Study *(please tick all the relevant boxes which apply)*   Adverse Drug Reaction/Drug Safety Drug Use  Disease Epidemiology x  Drug Effectiveness  Pharmacoeconomic  Other |
| 1. This study is intended for:   Publication in peer reviewed journals x Presentation at scientific conference x  Presentation at company/institutional meetings  Other: Expert invited Meetings at UK Government and European Scientific Meetings |

| 1. Does this protocol also seek access to data held under the CPRD Data Linkage Scheme?   Yes x No |
| --- |
| 1. If you are seeking access to data held under the CPRD Data Linkage Scheme*, please select the source(s) of linked data being requested.   Hospital Episode Statistics  Cancer Registry Data**  MINAP x ONS Mortality Data  Index of Multiple Deprivation/ Townsend Score  Mother Baby Link  Other: (please specify)  ** As part of the ISAC review of linkages, the protocol may be shared - in confidence - with a representative of the requested linked data set(s) and summary details may be shared - in confidence - with the Confidentiality Advisory Group of the Health Research Authority.*  ***Please note that applicants seeking access to cancer registry data must provide consent for publication of their study title and study institution on the UK Cancer Registry website. Please contact the CPRD Research Team on [contact] or email* [*[contact]*](mailto:[contact]) *to discuss this requirement further.* |
| 1. If you are seeking access to data held under the CPRD Data Linkage Scheme, have you already discussed your request with a member of the Research team?   Yes x No*  **Please contact the CPRD Research Team on [contact] or email* [*[contact]*](mailto:[contact]) *to discuss your requirements before submitting your application.*  Please list below the name of the person/s at the CPRD with whom you have discussed your request.  [name] |
| 1. If you are seeking access to data held under the CPRD Data Linkage Scheme, please provide the following information:   The number of linked datasets requested: CPRD with ONS mortality register  A synopsis of the purpose(s) for which the linkages are required:  Death certificate/ cause of death information      Is linkage to a local dataset with <1 million patients being requested?  Yes*  No x  ** If yes, please provide further details:* |
| 1. If you have requested linked data sets, please indicate whether the Principal Investigator or any of the collaborators listed in response to question 5 above, have access to any of the linked datasets in a patient identifiable form, or associated with a patient index.   Yes*  No x  ** If yes, please provide further details:* |
| 1. Does this protocol involve requesting any additional information from GPs?   Yes*  No x  * *Please indicate what will be required:*  Completion of questionnaires by the GP*^ψ^* Yes  No  Provision of anonymised records (e.g. hospital discharge summaries) Yes  No  Other (please describe)  *^ψ^ Any questionnaire for completion by GPs or other health care professional must be approved by ISAC before circulation for completion.* |
| 1. Does this protocol describe a purely observational study using CPRD data (this may include the review of anonymised free text)?   Yes* x No**  ** Yes: If you will be using data obtained from the CPRD Group, this study does not require separate ethics approval from an NHS Research Ethics Committee.*  *** No: You may need to seek separate ethics approval from an NHS Research Ethics Committee for this study. The ISAC will provide advice on whether this may be needed.* |
| 1. Does this study involve linking to patient *identifiable* data from other sources?   Yes  No x |
| 1. Does this study require contact with patients in order for them to complete a questionnaire?   Yes  No x  *N.B. Any questionnaire for completion by patients must be approved by ISAC before circulation for completion.* |
| 1. Does this study require contact with patients in order to collect a sample?   Yes*  No x  ** Please state what will be collected* |

| 1. Experience/expertise available   Please complete the following questions to indicate the experience/expertise available within the team of researchers actively involved in the proposed research, including analysis of data and interpretation of results |
| --- |
| Previous GPRD/CPRD Studies Publications using GPRD/CPRD data  None  1-3 x x  > 3 |
| Yes No  Is statistical expertise available within the research team? x  *If yes, please outline level of experience* *Professor of Medical Statistics*  *And RA in statistics*  Is experience of handling large data sets (>1 million records)  available within the research team? x  *If yes, please outline level of experience* *Previous GPRD experience*  Is UK primary care experience available within the research team? x  *If yes, please outline level of experience* *Professor of Primary Care Epidemiology & Link to NIHR School of Primary Care Research* |
| 1. References relating to your study   Please list up to 3 references (most relevant) relating to your proposed study.  Cornish R, Macleod J, Strang J, Vickerman P, Hickman M. Risk of death during and after opiate substitution treatment in primary care: prospective observational study in UK general practice research database. BMJ 2010;341:c5475.  Degenhardt L, Randall D, Hall W, Law M, Butler T, Burns L. Mortality among clients of a state-wide opioid pharmacotherapy program over 20 years: risk factors and lives saved. Drug Alcohol Depend 2009 November 1;105(1-2):9-15.  McCowan C, Kidd B, Fahey T. Factors associated with mortality in Scottish patients receiving methadone in primary care: retrospective cohort study. BMJ 2009;338(doi: 10.1136/bmj.b2225.). |

**Protocol content checklist**

In order to help ensure that protocols submitted for review contain adequate information for protocol evaluation, ISAC have produced instructions on the content of protocols for research using CPRD data. These instructions are available on the CPRD website ([www.cprd.com/ISAC](http://www.cprd.com/ISAC)). All protocols using CPRD data which are submitted for review by ISAC must contain information on the areas detailed in the instructions. IF you do not feel that a specific area required by ISAC is relevant for your protocol, you will need to justify this decision to ISAC.

Applicants must complete the checklist below to confirm that the protocol being submitted includes all the areas required by ISAC, or to provide justification where a required area is not considered to be relevant for a specific protocol. Protocols will not be circulated to ISAC for review until the checklist has been completed by the applicant.

**Please note, your protocol will be returned to you if you do not complete this checklist, or if you answer ‘no’ and fail to include justification for the omission of any required area.**

|  | **Included in protocol?** | |  |
| --- | --- | --- | --- |
| Required area | Yes | No | If no, reason for omission |
| *Lay Summary (max.200 words)* | x |  |  |
| *Background* | x |  |  |
| *Objective, specific aims and rationale* | x |  |  |
| *Study Type*  *Descriptive*  *Hypothesis Generating*  *Hypothesis Testing* | x  x  x |  |  |
| *Study Design* | x |  |  |
| *Sample size/power calculation*  *(Please provide justification of*  *sample size in the protocol)* | x |  |  |
| *Study population*  *(including estimate of expected number of*  *relevant patients in the CPRD)* | x |  |  |
| *Selection of comparison group(s) or controls* | x |  |  |
| *Exposures, outcomes and covariates*  *Exposures are clearly described*  *Outcomes are clearly described* | x  x  x |  |  |
| *Use of linked data*  *(if applicable)* | x |  |  |
| *Data/ Statistical Analysis Plan*  *There is plan for addressing confounding*  *There is a plan for addressing missing data* | x  x  x |  |  |
| *Patient/ user group involvement ^†^* | x |  |  |
| *Limitations of the study design, data sources*  *and analytic methods* | x |  |  |
| *Plans for disseminating and communicating study results* | x |  |  |

***^†^ It is expected that many studies will benefit from the involvement of patient or user groups in their planning and refinement, and/or in the interpretation of the results and plans for further work. This is particularly, but not exclusively true of studies with interests in the impact on quality of life. Please indicate whether or not you intend to engage patients in any of the ways mentioned above.***

***Voluntary registration of ISAC approved studies:***

*Epidemiological studies are increasingly being included in registries of research around the world, including those primarily set up for clinical trials. To increase awareness amongst researchers of ongoing research, ISAC encourages voluntary registration of epidemiological research conducted using MHRA databases. This will not replace information on ISAC approved protocols that may be published in its summary minutes or annual report. It is for the applicant to determine the most appropriate registry for their study. Please inform the ISAC secretariat that you have registered a protocol and provide the location.*

**HS&DR Project: 12/136/105** - Evaluating the impact of opiate substitution treatment on drug related deaths in the population: a natural experiment using primary care, other drug treatment databases & model projections: **ISAC CPRD Protocol 14_073R2** (AMENDMENT 27/10/2014)

**Lay Summary**

People who inject drugs (PWID) such as heroin have a risk of death >10 times higher than the general population. Overdose is the most common cause of death among PWID. The most effective treatment for heroin injectors is the prescription of legal, non-injected substitute drugs, most commonly methadone or buprenorphine. This is called opiate substitution treatment (OST) and in the UK is delivered mainly in primary care. Several recent studies have highlighted that there is a period of very high mortality risk in the first few months immediately after treatment cessation. In the UK OST prescription has expanded 5-fold in the last 10 years, but we have not observed any commensurate decrease in the number of drug related deaths in the population. This apparent paradox motivates our research i.e could the benefits of drug treatment be outweighed or balanced out by other factors which increase the risk of drug related deaths during or after OST? We will conduct a “natural experiment” and test our hypothesis by analysing data of people on OST and other drug treatments in the community and model how changes in the way drug treatment is delivered could reduce drug related deaths in the population.

**Background**

Opiate substitution treatment (OST) is the key treatment for heroin dependence and has been shown to have multiple benefits, including reductions in drug related crime, blood borne virus transmission, and improvements in social functioning(1-5). Prescribed OST in the community includes methadone, buprenorphine, and dihydrocodeine(1, 6). There are approximately 200,000 people who inject drugs (PWID), half exposed to drug treatment annually, mainly OST (75%) but also non-pharmacological treatments delivered in specialist drug agencies and residential units. OST is effective because it reduces heroin injection and is cost effective because of reductions in drug related crime and health harms(7). Observational studies have shown that the risk of mortality is reduced during opiate substitute treatment(8-12). Buprenorphine has been shown to be as good as methadone at treatment retention(13), and hypothetically is less likely to cause fatal overdose than methadone(14). In France, ecological analyses suggest that trends in overdose deaths are negatively associated with increases in buprenorphine prescription(15). However, direct comparative evidence on the risk of death during buprenorphine vs. methadone is yet to emerge.

Several recent studies also have highlighted that there is a period of very high mortality risk (>8 times higher than mortality risk during treatment) in the first few months immediately after treatment cessation (9-11, 16). In the UK analyses of primary care information have suggested that the risk of death in those who receive OST is twice as high among men compared to women, and is raised at the beginning and end of treatment, and maybe higher in those co-prescribed benzodiazepines(11, 17). In Australia the risk of death at treatment onset was greater than in the UK, with some evidence to suggest that the mortality risk at treatment onset was lower among those initiated onto buprenorphine compared to methadone, but these benefits may be offset by a shorter duration of treatment for those on buprenorphine compared to methadone(9). The evidence base on other drug treatments (residential rehabilitation, detoxification, and psychological treatments) is more limited; but studies also suggest that the risk of mortality is reduced during treatment and elevated after treatment (10, 18).

In the UK OST has expanded 5-fold in the last 10 years to over 1800kg per year (roughly equivalent to 33.3 million doses per year)(19). The rate of methadone deaths per gram of methadone prescribed has fallen, coinciding and attributed to the issuing and implementation of clinical guidelines recommending greater supervised consumption(20), but trends in the overall number of opiate related deaths have not declined (21) (22). Therefore, we aim to examine in more detail the risk of death during and after OST and other drug treatment in order to assess how changing the delivery of drug treatment could reduce the number of drug related deaths in the population.

**Objective, specific aims and rationale**

Our over-arching hypotheses are that the impact of opiate substitution treatment (OST) and other drug treatments in reducing drug related death (DRD) is influenced by modifiable treatment related factors (such as treatment duration, co-prescription of other drugs, treatment modality and dose, and dispensing arrangements); and that currently the benefits of OST and other non-pharmacological treatments in reducing drug related deaths in the population maybe outweighed or balanced out by other factors which increase risk of mortality.

The aim of the study, therefore, is to corroborate or refute these hypotheses in order to inform robust, credible evidence based treatment guidelines that can underpin the effective reduction of population drug-related deaths through primary care based intervention. This project will focus on the analysis of OST delivered in primary care through the analysis data from the Clinical Practice Research Datalink (a parallel project will analyse non-pharmacological treatments reported to National Drug Misuse Database held in the Drug Data Warehouse, DDW). These analyses from CPRD and DDW will be combined in a mathematical model of drug related mortality and drug treatment.

We will determine the risk of OD and death by treatment exposure and modality, relate these effects to the number of OD deaths and coverage and duration of drug treatment in the community, and project what factors could reduce the number of drug related deaths in the population.

Additional questions to be addressed include:-

- Is there a difference in the risk of mortality between prescribed methadone or buprenorphine?
- Is the risk of fatal overdose (OD) increased in people that are co-prescribed benzodiazepines?
- Is the risk of OD and mortality during and after residential, detoxification and non-pharmacological treatments similar to OST?
- Is the risk of OD and drug related death at treatment onset and cessation reduced in patients with evidence of supervised consumption and planned discharge?
- Is there evidence that delivery of OST in primary care has changed over time in terms of average dose, modality, duration, co-prescription of benzodiazepines, evidence of planned discharge and supervised consumption?
- Is there evidence that delivery of OST in primary care has changed over time – specifically in terms of changes in:- average dose and % of patients receiving optimal OST dose; OST modality; number and % of patients undergoing a planned discharged over time; number and % receiving co-prescription of benzodiazepines; number and % with evidence of supervised consumption.

**Study Type**

The study is observational and hypothesis testing (see aims/objectives above).

**Study Design**

We are conducting an observational “natural experiment” study and developing a policy impact model. The key intervention – Opiate Substitution Treatment (OST) can no longer be randomised with a placebo control, and no earlier trials of OST were large enough to assess mortality as the outcome(3). Therefore, we are exploiting information (that was not collected specifically for research) on variation in exposure and outcome derived from administrative databases. We will extract and analyse an open observational cohort based on Clinical Practice Research Datalink (CPRD) primary care database.

**Sample size/power calculation**

The main analysis is on opiate substation treatment (OST) in primary care and risk of death and in particular the comparison of methadone and buprenorphine*.

There will be at least 20,000 OST patients (extracted from CPRD GOLD patients) from 1998 to 2014 linked to NHS central registry and ONS mortality data, that will generate 67,000 person years (pys) follow-up (~32,000 on treatment and ~35,000 off) if censored 12 months after last OST. There will be over 700 deaths of which ~500 will be due to overdose. This will be the largest study in the UK with precise data on OST treatment exposure (including ~ 12000 pys on buprenorphine and 30,000pys on methadone). In addition, there will be approximately 10,000 and 12,000 person years in treatments lasting less than 1 month or greater than 12 months, and 3000 and 1200 person years follow-up in the first 4 weeks treatment on or immediately after methadone or buprenorphine treatment respectively.

Thus, there is sufficient power (> 90%) to determine whether:-

1. there is at least a halving of the risk of death during treatment on burpenorphine compared to methadone (i.e. 0.35% vs. 0.69% respectively) – which requires a sample of at least 922 in each group compared to 12,000 and 20,000 on buprenorophine and methadone
2. and sufficient power (80%) to test if the risk of death is at least a 1/3 lower on buprenorphine at (0.006%) compared to methadone (0.016%) in the first 4 weeks of treatment (1200 and 3000 person years respectively) – as indicated by unpublished analyses by Degenhardt on Australian mortality cohort(9).

In addition, there is sufficient power to corroborate that the risk of fatal overdose out of treatment at 0.8% is twice as high as the risk during treatment – which will require sample of at least 788 in and out of treatment compared to our sample of over 30,000 person years in each group; and that the risk of death in the 4 weeks after treatment at about 4.6% is 1/3 lower (3.0%) for people treated for short duration of treatment (< 1 month) compared to those treated for 12 months or longer – which will require sample of at least 3123 in each group compared to over 3500 and 3850 person years among those exposed to short or prolonged treatment respectively;

[In addition, the DDW linked mortality file has over 50,000 patients exposed to other structured non-pharmacological drug treatments, with around 44,000 pys of observation, from 2005 to 2009, and therefore also has sufficient power to test for differences in the risk of death in different periods during and after drug treatment.]

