**Use of linked data**

We will use the ONS mortality file to define overdose and drug related mortality. Previously supplied data in 2014 provided fewer deaths than expected with only 30% of deaths in the OST sample being identified as overdose or drug related. This left analyses underpowered to detect expected effect sizes. The new linkage data, set 11 covering a greater number of practices and a longer time span, offers the potential to overcome the limitations of our current data set.

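### The expected ~500 overdose deaths do not follow from the protocol's own overdose risks and person-years, which give about 408, and the linked sample size of 788 matches risks ten times those stated

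*Protocol*

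**What the plan says.** All the figures are in the Protocol, Sample size/power calculation.

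- Follow-up: "67,000 person years (pys) follow-up (~32,000 on treatment and ~35,000 off) if censored 12 months after last OST".
- Events: "There will be over 700 deaths of which ~500 will be due to overdose".
- Risks, in the paragraph after the numbered list: "the risk of fatal overdose out of treatment at 0.8% is twice as high as the risk during treatment".
- Sample size for that comparison: it "will require sample of at least 788 in and out of treatment compared to our sample of over 30,000 person years in each group".
- The same sentence goes on to a separate figure for early time off treatment: "the risk of death in the 4 weeks after treatment at about 4.6" per cent. This is a risk of death, not of overdose.

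The section does not say how ~500 was obtained. It also does not say whether 0.8% covers all time off treatment or only the time after the first 4 weeks. The Exposures, outcomes and covariates section divides off-treatment time into those two periods and singles out drug poisoning or overdose within the main outcome.

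**The concern.** The section gives both an expected number of overdose deaths and everything needed to compute one: a risk off treatment, its ratio to the risk on treatment, and the person-years in each state. The protocol itself sets these risks against person-years, so multiplying them follows its own usage. The product should come close to ~500, and it does not.

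The expected count is what a reader uses to judge how precisely overdose mortality can be estimated, by treatment period and by drug. It is also the natural yardstick for the amendment of 9 December 2015 (Use of linked data), which reports "fewer deaths than expected with only 30% of deaths in the OST sample being identified as overdose" or drug related. Depending on which figures are used, the expected overdose share of 700 deaths is 58% or 71%, so the protocol does not offer one clear expectation.

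**Working it through.** **Inputs** (Protocol, Sample size/power calculation): 35,000 person-years off and 32,000 on treatment; overdose risk 0.8% off treatment; on-treatment risk half of that, 0.4% (derived); stated deaths 700, of which 500 overdose.

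**1. Stated share.** 500 / 700 = 71%.

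**2. Expected overdose deaths = risk x person-years, summed.**
- Off: 0.008 x 35,000 = 280
- On: 0.004 x 32,000 = 128
- Total: 408, which is 58% of 700. The stated figure is 500 / 408 = 1.23 times this.

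**3. Could rounding explain it?** Let 0.8% stand for anything from 0.75% to 0.85%, keeping the ratio of two.
- Low: 0.0075 x 35,000 + 0.00375 x 32,000 = 262.5 + 120 = 382.5
- High: 0.0085 x 35,000 + 0.00425 x 32,000 = 297.5 + 136 = 433.5

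The range of 383 to 434 does not reach 500.

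**4. Risks that would give 500 with the ratio of two kept.** Solve r x 35,000 + (r/2) x 32,000 = 500. Then r = 500 / 51,000 = 0.98% off treatment and 0.49% on treatment.

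**5. Sample size in the same sentence.** Two-proportion formula, two-sided 0.05 and 90% power. The protocol states no significance level, and no power level for this comparison.

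n = [1.96 x sqrt(2 p q) + 1.2816 x sqrt(p1 q1 + p2 q2)]^2 / (p1 - p2)^2, where p is the mean of p1 and p2 and each q is one minus the matching p. The continuity correction is n' = (n/4) x [1 + sqrt(1 + 4 / (n (p1 - p2)))]^2.

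| Risks compared | n per group | n' with continuity correction |
|---|---|---|
| 8% vs 4% | 739 | 788 |
| 0.8% vs 0.4% | 7,832 | 8,324 |

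The stated 788 is reproduced exactly by risks ten times those in the text.

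**6. Effect on the on/off comparison.** With 32,000 and 35,000 person-years treated as sample sizes, power for 0.4% vs 0.8% exceeds 99.9%. These inputs are the ones that imply 408 events.

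**7. Effect on precision.** If 408 is the right count, standard errors of log rates scale by about sqrt(500 / 408) = 1.11, so they are roughly 11% larger than ~500 events would suggest.

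**The case against.** The best defence is that 0.8% may describe only the time after the first 4 weeks off treatment. The protocol separates those periods and gives a much higher early risk of 4.6%. Suppose the early window holds between 2,100 and 4,200 person-years; this is an assumed split of the 3,000 + 1,200 that the section gives for 4-week windows, whose wording is ambiguous.

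- Every early death counted as overdose: 0.046 x 2,100 + 0.008 x 32,900 + 128 = 488, up to 0.046 x 4,200 + 0.008 x 30,800 + 128 = 568.
- Only 5/7 of early deaths counted (the 500/700 share): 460 to 512.

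These ranges include ~500. There is also some internal support. The first numbered power item gives 0.0035 x 12,000 + 0.0069 x 20,000 = 42 + 138 = 180 deaths on treatment. The 128 on-treatment overdoses are 71% of these, the same share as 500/700.

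What stands is that ~500 may be right and the stated off-treatment risk incomplete. What does not stand is that this removes the mismatch. The text says out of treatment without any exclusion, the 4.6% is all-cause, and the person-years have to be assumed. The reading also breaks another stated figure. Over all 35,000 off-treatment person-years the overdose rate becomes 0.95% to 1.26%, which is 2.4 to 3.1 times 0.4%, not twice. If this was the intention, the text has to say so.

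It is also fair to object that no power statement uses ~500, and that the key buprenorphine versus methadone calculation rests on other inputs. Both points are correct, and they limit the consequence.

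**Conclusion.** The stated ~500 overdose deaths do not follow from the stated risks and person-years, which give about 408 (383 to 434 with rounding). This assumes that 0.8% applies to all off-treatment time and that the on-treatment risk is half of it, which is the plain reading. The 788 is a tenfold slip in the risks; the corrected requirement of about 8,324 is still met. The issue concerns the event count and the precision expected for overdose death, not the power of the on/off comparison.

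Four stronger readings are tempting but not supported:

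- *The count is overstated by 23%.* The ratio is right, but nothing shows that the count, rather than the risks, is the wrong figure.
- *The off-treatment risk should be 1.06%.* (500 - 128) / 35,000 = 1.06% holds the on-treatment risk at 0.4%. The ratio then becomes 2.7, against the stated two.
- *On-treatment time is really 42,000 person-years, giving 448.* The section does say "including ~ 12000 pys on buprenorphine and 30,000pys on methadone", but 42,000 + 35,000 = 77,000 exceeds the stated total of 67,000. The first power item's 12,000 + 20,000 agrees with 32,000.
- *Part of the shortfall reported in the 2015 amendment comes from this figure.* The amendment gives neither the observed count nor the expectation it was measured against, and 30% is far below both 58% and 71%.

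**What to change.** In the Protocol, Sample size/power calculation, show how the expected overdose deaths were derived and reconcile them with the risks in one of three ways:

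1. If the risks are right, state about 410 expected overdose deaths (about 58% of 700).
2. If ~500 is right, restate the risks that produce it: about 0.98% off and 0.49% on treatment if the ratio of two is kept.
3. If 0.8% applies only after the first 4 weeks off treatment, say so, give the overdose rate and person-years for those 4 weeks separately, and restate the overall off/on ratio.

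Replace 788 with the number for the risks finally stated (about 8,324 per group for 0.8% vs 0.4%), and give the significance level, the power and the use of a continuity correction.

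The cost is a few figures and one or two sentences. The design, the data request and the analyses do not change. Under the first option the expected event count becomes less favourable.

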**Use of linked data**

We will use link to ONS mortality file for our outcome measures. **Data/ Statistical Analysis Plan**

1) We expect that overdose and drug related mortality risk differs by period of treatment exposure (1-4 weeks treatment start, rest of treatment duration, 1-4 weeks treatment end, 5-52 weeks out of treatment). The main analysis will test whether there is evidence of a difference in mortality risk by modality of OST (methadone vs. buprenorphine) at different periods on and off treatment – and will investigate also mortality risk in relation to additional exposures (co-prescription of benzodiazepines, measures of treatment performance/quality) and confounders (age, gender, co-morbidity as defined by Charlson Index(24), alcohol and mental health problems, treatment episode number, calendar year) all of which have been shown to influence mortality risk(11) (9). However, other potential confounders or factors relating to injecting risk may be missing or incompletely measured in CRPD (such as crack-cocaine use).

We will undertake a series of analyses that aim to incorporate and adjust for confounding.

First, we will use Poisson regression incorporating time varying covariates (such as co-prescription of benzodiazepines, episode and duration of treatment) to describe mortality risks and compare these at different periods on and off treatment and by modality of OST. These analyses will generate incidence rate ratios (IRR) that compare mortality risk for patients on methadone (from week 4 to end of treatment as baseline) to other periods and other forms of OST; will compare mortality rate for key confounders (above); adjust IRR by period on or off treatment for these confounders; and examine specifically whether co-prescription of benzodiazpeines increases the risk of mortality during and after treatment.

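### The 80% power claimed for the first 4 weeks of treatment rests on person-years that the protocol labels in two different ways, and it cannot be reproduced from the printed rates

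*Protocol*

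**What the plan says.** In the Sample size/power calculation section, the description of expected follow-up ends with "3000 and 1200 person years follow-up in the first 4 weeks treatment on or immediately after methadone or buprenorphine treatment respectively". That label covers two windows, the weeks after starting and the weeks after stopping.

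Item 2 of the power list claims "sufficient power (80%) to test if the risk of death" differs between the drugs, specifically whether "the risk of death is at least a 1/3 lower on buprenorphine at (0.006%) compared to methadone (0.016"%), and gives the exposure as "in the first 4 weeks of treatment (1200 and 3000 person years respectively"). The numbers are the same, but this label covers the starting window only.

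Point 1 of the Data/Statistical Analysis Plan divides time into "1-4 weeks treatment start, rest of treatment duration, 1-4 weeks treatment end, 5-52 weeks out of treatment". It makes methadone against buprenorphine by period the main analysis.

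The last power statement in the section concerns death in the 4 weeks after treatment by treatment duration. It sets its requirement against an available exposure "compared to over 3500 and 3850 person years among those exposed to short or prolonged treatment respectively".

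**The concern.** If the 3,000 and 1,200 person-years pool the two windows, item 2 counts follow-up that the analysis will assign to a different period, and the onset comparison has less information than stated. If they apply to each window, the exposure in item 2 is right and only the wording is loose. The protocol does not say which.

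This matters because the Limitations section names the safety of buprenorphine relative to methadone as the key hypothesis, and item 2 is the only power statement for that contrast at treatment onset. A reader will use the 80% to judge how much weight a null onset result can bear.

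**Working it through.** **Inputs, all from Sample size/power calculation.** Person-years: 1,200 buprenorphine, 3,000 methadone (ratio 2.5). Rates as printed: 0.006% and 0.016%. Claimed power: 80%. Patients: at least 20,000. Alpha is not stated.

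**Step 1: settle alpha.** For the post-treatment comparison (3.0% against 4.6%) I used n = [1.96√(2p̄(1−p̄)) + 1.2816√(p₁(1−p₁)+p₂(1−p₂))]² / (p₁−p₂)², which gives 2,999 per group. The continuity correction n/4·[1+√(1+4/(n|p₁−p₂|))]² gives 3,123, which is the protocol's figure ("which will require sample of at least 3123 in each group"). Two-sided 5% is therefore a fair assumption for item 2.

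**Step 2: item 2 at the printed rates, full exposure.** Power = Φ[(|p₁−p₂| − 1.96·s₀)/s₁], where s₀ is the standard error under a pooled rate and s₁ the standard error under the two separate rates.
- Expected deaths: 1,200 × 0.00006 = 0.07 and 3,000 × 0.00016 = 0.48.
- s₀ = 0.000392, s₁ = 0.000321; (0.000100 − 0.000767)/0.000321 = −2.08; power about 2%.
- An exact conditional test has essentially no power with about half a death expected in total.
- Reaching 80% would take about 129,000 buprenorphine and 323,000 methadone person-years.

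The 80% is not reproduced.

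**Step 3: rates re-read as 0.006 and 0.016 per person-year (0.6% and 1.6%), full exposure.**
- Expected deaths: 7.2 and 48.
- s₀ = 0.003890, s₁ = 0.003197; (0.010000 − 0.007624)/0.003197 = 0.743; power 77%.
- Exact conditional test: given the total, buprenorphine deaths are binomial with probability 1,200/4,200 = 0.286 under the null and 7.2/55.2 = 0.130 under the alternative. Averaged over a Poisson total with mean 55.2, power is 75%.

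**Step 4: same re-read rates, by assumed onset share of the exposure.**

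| Onset share (assumed) | Person-years, bup / meth | Expected deaths | Pooled test | Exact test |
|---|---|---|---|---|
| All | 1,200 / 3,000 | 7.2 / 48 | 77% | 75% |
| 75% | 900 / 2,250 | 5.4 / 36 | 63% | 60% |
| Two thirds | 800 / 2,000 | 4.8 / 32 | 57% | 54% |
| Half | 600 / 1,500 | 3.6 / 24 | 43% | 39% |

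**Step 5: can the document settle the split?**
- 3,000 + 1,200 = 4,200 person-years. At 13 four-week windows a year that is 54,600 full windows, or 2.7 per patient in 20,000. With repeated episodes this excludes neither reading.
- 3,500 + 3,850 = 7,350 person-years are set against the 4 weeks after treatment. That is 95,550 windows, or 4.8 per patient, from two duration classes only. It exceeds 4,200 whether 4,200 is one window or two.

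No split can be inferred.

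**Side check on the effect size.** 0.006/0.016 = 0.375, a 62.5% reduction, not one third. A true one-third reduction from 1.6% has pooled-test power of 24% with the full exposure and 13% with half.

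**The case against.** The strongest defence is that the phrase can be read distributively, as 3,000 and 1,200 person-years in each window. Item 2, which uses them as onset time, supports that reading. There is then no exposure error, and with rates of 0.6% and 1.6% power is close to the claim: 77% pooled, 75% exact, and 80% with a two-sided mid-p exact test. One-sided testing (87% pooled) or an events-only approximation (91%) would exceed it. This stands as far as it goes. It shows that 80% may have been a reasonable rounding under one set of intentions. It does not make the figure derivable from what is printed, because it still needs a 100-fold change of rate scale and a choice between two labels.

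A reader might go further and infer that only half the exposure is onset time and that the true power is near 40%. The documents do not support that. The equal split is nowhere stated, the 7,350 post-treatment person-years do not fit a pooled 4,200, and the 39-43% also needs the re-read rates. At the printed rates, halving the exposure moves pooled power only from about 2% to about 1.5%, so exposure is not why the 80% fails there. Nor is the rate scale settled by analogy. Two other sample sizes in the section (788 and 922) reproduce only at risks ten times those printed, but a ten-fold change here (0.06% against 0.16%) gives 8% at full exposure.

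It can also be said that the December 2015 amendment already concedes low power and moves to a larger linkage. It does, but it gives no revised figure for item 2.

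**Conclusion.** The point holds as a defect of definition and reproducibility. The same two exposure figures carry two labels, the power claim uses all of them as onset time, and the analysis keeps the two windows apart. The claimed 80% is not reproduced by the pooled or exact conditional two-sided 5% test under either reading of the exposure. Power is about 2% or less at the printed rates, and 75-77% at best if the rates mean 0.6% and 1.6%. On that second reading, the fall to 60-63%, 54-57% or 39-43% depends entirely on an onset share that the protocol does not give. The rate scale is the larger fault in the same line. The exposure label is a separate one and would remain after the scale was corrected.

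**What to change.** Replace the two exposure figures with four: person-years in weeks 1-4 on treatment and in weeks 1-4 after treatment, each for methadone and for buprenorphine. Reconcile the after-treatment figures with the 3,500 and 3,850 person-years used for the duration comparison. State whether the item 2 rates are percentages or rates per person-year, and make the one-third wording agree with them. Then recompute item 2 on onset person-years only, naming the test, alpha and sidedness, and using the linkage set now planned under the December 2015 amendment rather than the extract it replaces. Put the resulting power, or the detectable rate ratio, in place of 80%. A figure near 40% should not be entered unless the tabulated split and the stated rate scale lead to it.

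The cost is one tabulation and a short recalculation, with no new patients. The drawback for the sponsor is that the stated power will probably be lower.
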